**Abbreviations**

|        |                                             |
|--------|---------------------------------------------|
| BARC   | Bleeding Academic Research Consortium       |
| CABG   | Coronary artery bypass surgery              |
| CEC    | Clinical Endpoints Committee                |
| CI     | Confidence interval                         |
| COPD   | Chronic obstructive pulmonary disease       |
| CV     | Cardiovascular                              |
| Cx     | Circumflex                                  |
| DMC    | Data monitoring committee                   |
| HR     | Hazard Ratio                                |
| IQR    | Interquartile range                         |
| LAD    | Left anterior descending                    |
| MI     | Myocardial infarction                       |
| MINAP  | Myocardial ischaemia national audit project |
| NSTEMI | Non-ST elevation myocardial infarction      |
| ONS    | Office for National Statistics              |
| PCI    | Percutaneous coronary intervention          |
| RCA    | Right coronary artery                       |
| RMST   | Restricted mean survival time               |
| SAP    | Statistical Analysis Plan                   |
| SAUC   | Standardised area under the curve           |
| SD     | Standard deviation                          |
| SVG    | Saphenous vein graft                        |
| TIA    | Transient ischaemic attack                  |
| TMF    | Trial Master File                           |
| TMG    | Trial Management Group                      |
| TSC    | Trial Steering Committee                    |
| ULN    | Upper limit of normal                       |

# 1. INTRODUCTION

## 1.1 Background and rational

Heart disease, in particular coronary artery disease, remains one of the leading causes of death in the UK and worldwide. As our population ages, increasing numbers of older patients are presenting with coronary artery disease, including non-ST elevation myocardial infarction (NSTEMI).

Older patients admitted after an episode of NSTEMI are often frail, with up to a third of older patients ( $\geq 75$  years) being severely frail. These frail older patients are often denied routine invasive strategy (coronary angiography with a view to coronary revascularisation by percutaneous coronary intervention (PCI) or coronary artery bypass surgery (CABG)) due to fear of complications and causing harm. Whether these procedures are beneficial in older patients, in particular those with co-morbidities and those who are frail, is unknown.

This study aims to determine the benefit and risks of routine invasive strategy (coronary angiography+/-revascularisation and optimal medical therapy) versus conservative management (optimal medical therapy only) in older patients aged 75 years or over presenting with NSTEMI.

## 1.2 Objectives

### Primary

To determine the impact of a routine invasive strategy on cardiovascular death and non-fatal myocardial infarction (MI) compared with a conservative treatment strategy in older patients ( $\geq 75$  years) presenting with NSTEMI.

### Secondary Objectives

To determine the impact of a routine invasive strategy compared with a conservative strategy on:

- All-cause death
- Cardiovascular death
- Non-cardiovascular death
- Recurrent myocardial infarction
- Coronary angiography and coronary revascularisation
- Hospitalisation for heart failure
- Stroke
- Transient ischaemic attack (TIA)
- Bleeding (Bleeding Academic Research Consortium (BARC)  $\geq 2$ )
- Procedural and in-hospital complications
- Frailty
- Length of time spent at home
- Quality of life (outside the scope of this analysis plan\*).
- Cost-effectiveness (outside the scope of this analysis plan\*).

\*Methods for the analysis and reporting of quality of life as assessed by EQ-5D-5L and cost-effectiveness will be documented in a Health Economics Analysis Plan (HEAP). See the current version of the HEAP for more details.

## 2. STUDY METHODS

### 2.1 Trial design

SENIOR-RITA is a multicentre, prospective, phase III, open-label trial in older patients (aged  $\geq 75$  years) presenting with type 1 NSTEMI. The trial aims to assess the impact of a routine invasive strategy on cardiovascular death and non-fatal myocardial infarction (MI) compared with a conservative treatment strategy. All patients will be randomised (1:1) to receive invasive (coronary angiography  $\pm$  coronary revascularisation plus optimal medical therapy) or conservative strategy (optimal medical therapy alone). For patients randomised to the invasive strategy, invasive coronary angiography will be performed as per local practice with coronary revascularisation by PCI or CABG performed based on angiographic findings at the discretion of the attending cardiologist and the local multidisciplinary team.

Patients will be followed-up for at least one year after the last patient has been recruited, up to a maximum of 5 years. In the future, longer-term follow-up data is planned to be collected up to 10 years using record linkage to electronic medical records (e.g. via Office for National Statistics (ONS), Hospital Episode Statistics and Scottish Health data).

### 2.2 Study setting and patient population

This is a broad and inclusive trial that includes all-comer older patients (aged  $\geq 75$  years) with NSTEMI, including those with co-morbidities and/or cognitive impairment\* in whom there is currently a lack of evidence relating to the management of NSTEMI. Patients are being recruited from ~52 NHS centres throughout the UK.

#### Inclusion Criteria

- Aged  $\geq 75$  years
- Type 1 NSTEMI during index hospitalisation

#### Exclusion Criteria

- Patients presenting with STEMI or unstable angina
- Patients with cardiogenic shock
- Patients with known life expectancy  $< 1$  year
- Patients in whom neither the patient nor the consultee are able and willing to provide written informed consent
- Previous inclusion in the BHF SENIOR-RITA trial
- Inability to undergo invasive coronary angiography, such as no vascular access site, or absolute contraindication to coronary revascularisation.

*\*Note that patients lacking capacity to provide informed consent will not be approached at Scottish sites due to different mental capacity act in Scotland and due to lack of ethics approval in Scotland to approach cognitively impaired patients.*

## 2.3 Randomisation and blinding

Patients are randomised to invasive or conservative management on a 1:1 basis using a variable-length block stratified method. Block lengths used are documented in the statistical section of the TMF. Randomisation is performed at site using a secure web-based system.

Up to 14th September 2018 stratification was based on three factors:

- Recruiting centre
- Frailty score: frail (Rockwood Frailty Score  $\geq 5$ ) and not frail (Rockwood Frailty Score  $< 5$ )
- Cognitive impairment: impaired (Montreal Cognitive Assessment (MoCA) score  $< 26$ ) and not impaired (MoCA  $\geq 26$ ).

At the time data were first presented to the data monitoring committee (DMC) on 30th June 2017, a small proportion (~7%) of patients were found to have been randomised to the incorrect cognitive impairment strata. At the time of the next DMC meeting, this had increased to ~13%. On investigation, it became apparent that some sites found it logistically challenging to obtain a complete 30-item MoCA assessment from the participant prior to randomisation. So as not to delay treatment, randomisation was going ahead without a complete MoCA assessment being carried out, with cognitive impairment judged by the treating clinician for the purpose of randomisation and the MoCA assessment completed after randomisation. This was leading to a number of protocol deviations.

The decision was therefore made to remove cognitive impairment as a stratification factor. This was incorporated into protocol version 2.0 [14/12/17]. However due to a delay in updating the randomisation system, this was not implemented in practice until 14th September 2018, following the implementation of all other aspects of protocol version 2.0 on 20th February 2018. In total, 532 participants were recruited under the original allocation strategy.

The update to the randomisation system involved creating new blocks of participants, with variable block lengths as before. Incomplete blocks using the old strata were not used. The overall sample size should ensure this change has minimal or negligible effect on the overall balance between randomised groups at the end of the study.

Due to the nature of the intervention, it is not possible to blind patients or clinicians to trial treatment. The trial statistician ([name]) has been involved in preparing unblind reports to the DMC. The senior statistician responsible for approving this Statistical Analysis Plan has not reviewed any unblind data by randomised treatment group and will remain blind until the data are locked for the primary analysis.

## 2.4 Definition of outcome measures

### Primary endpoint

The primary endpoint is time to cardiovascular (CV) death or non-fatal MI (of any type, defined by the fourth universal definition). This will be measured as the time from randomisation to date of CV death or non-fatal MI (whichever comes first). Patients alive and free from recurrent non-fatal MI at the time of analysis will be censored at the date they were last seen or assessed (latest date of follow-up / assessment on the Clinical Endpoint eCRF), up to a maximum of 5 years post randomisation. Patients free from recurrent non-fatal MI but experiencing non-CV death will be censored at their date of death.

All death and recurrent MI events will be reviewed and adjudicated, in a blinded fashion, by an independent Clinical Endpoints Committee (CEC) and it will be this assessment which will be used for the main analysis. Further details of the adjudication process can be found in the Clinical Endpoints Committee Charter.

Deaths will be considered cardiovascular in cause if the CEC adjudicates the cause of death as cardiovascular. In addition, while we do not anticipate there will be many deaths where the CEC cannot determine whether the participant died of a cardiovascular or non-cardiovascular cause (and will therefore be reported as undetermined), for the primary analysis these undetermined cases will be conservatively included as cardiovascular deaths. This will include cases where no source data or death certificate are available. Sensitivity analyses will be performed assuming undetermined deaths are non-cardiovascular.

For some MI events, it is possible insufficient source data will be available to allow the CEC to adjudicate the event, however we do not anticipate this to affect many cases. In such cases the event will be considered a MI, as per the local site assessment, and will be assumed to be Type 1. The number of MI events the CEC could not adjudicate will be reported. A fatal MI will be defined as cardiovascular death (as per CEC adjudication) within 30 days of MI (confirmed as per CEC adjudication, or as per local site assessment when insufficient source data is available). All other MIs will be considered non-fatal.

As a supplementary analysis we will also report a composite outcome of all-cause death and non-fatal MI. Time will be measured from randomisation to death from any cause or non-fatal MI, whichever is earliest. Patients alive and free from recurrent non-fatal MI will be censored at the date they were last seen or assessed.

### Secondary endpoints

For all secondary endpoints, timing of analyses will coincide with the main analysis of the primary endpoint.

#### All-cause death

This will be measured as the time from randomisation to the date of death. Patients alive at the time of analysis will be censored at the date they were last seen or assessed.

#### Cardiovascular death

This will be measured as the time from randomisation to date of cardiovascular death. Patients alive at the time of analysis will be censored at the date they were last seen or assessed. Patients experiencing non-CV death will be censored at their date of death. Cause of death will be as adjudicated by the CEC, with undetermined deaths assumed to be cardiovascular.

#### Non-cardiovascular death

This will be measured as the time from randomisation to date of non-cardiovascular death. Patients alive at the time of analysis will be censored at the date they were last seen or assessed. Patients

experiencing CV death will be censored at their date of death. Cause of death will be as adjudicated by the CEC.

#### Recurrent MI

All recurrent MIs (fatal and non-fatal) are reported in the database by site staff and adjudicated by the CEC using the fourth universal definition.

As a component of the primary outcome, time to first non-fatal MI will be reported. Time will be measured from randomisation. Patients known to have died and not experienced a recurrent non-fatal MI will be censored at their date of death. Patients alive and free from recurrent non-fatal MI will be censored at the date they were last seen or assessed.

The total number of recurrent MIs (non-fatal, fatal, and overall), and the total number of patients affected by recurrent MIs (non-fatal, fatal, and overall), will be calculated for each randomised group. The number of occurrences and number of patients affected by recurrent MIs of each type (as per the 4th Universal Definition; Type 1 / 2 / 3 / 4a / 4b / 4c / 5) will also be calculated. The number of MIs reported per participant will also be calculated.

A crude rate of all recurrent MI events (both fatal and non-fatal, of any type) will be calculated in each treatment group as the total number of recurrent MI events divided by the total patient follow-up time in each group.

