#### Recurrent MI, coronary angiography, coronary revascularisation, stroke, TIA, hospitalisation for heart failure

For each outcome measure, the number of participants reporting the event, the number of events per participant, and the total number of events (including multiple events per participant) will be tabulated by randomised group. The crude rate (total number of events or total follow up time) will also be reported alongside 95% CIs.

Time to non-fatal MI, time to first (non-trial) coronary angiography and time to first (non-trial) revascularisation will be estimated using Kaplan-Meier methods. Estimates of the treatment effect (HR) will be made using Cox regression models, as described above and reported with 95% CI's. The proportional hazards assumption will be assessed, and alternatives explored as previously described. Competing risks analyses will also be performed with death as the competing event, as per section 5.1.3.

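### The only between-arm time-to-event analysis of recurrent MI counts non-fatal MIs alone, so its hazard ratio depends on 30-day case fatality as well as on how often MI occurs

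*Supplement*

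**What the plan says.** Section 1.2 of SAP v2.0 lists "Recurrent myocardial infarction" among the secondary objectives, without limiting it to MIs that the patient survives.

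Section 2.4 (Primary endpoint) splits MIs by what follows them: "A fatal MI will be defined as cardiovascular death (as per CEC adjudication) within 30 days of MI". For the rest, "All other MIs will be considered non-fatal".

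Section 2.4 (Recurrent MI) then gives a time-to-event outcome for the non-fatal class: "As a component of the primary outcome, time to first non-fatal MI will be reported". On deaths it says: "Patients known to have died and not experienced a recurrent non-fatal MI will be censored at their date of death". Section 5.2 names the method, "Time to non-fatal MI, time to first (non-trial) coronary angiography and time to first (non-trial) revascularisation will be estimated using Kaplan-Meier methods", followed by Cox models adjusted for frailty. It adds: "Competing risks analyses will also be performed with death as the competing event, as per section 5.1.3". The example table of time-to-event outcomes has a row for non-fatal MI and none for MI of any kind.

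All MIs are summarised in other ways. Section 2.4 plans "The total number of recurrent MIs (non-fatal, fatal, and overall), and the total number of patients affected by recurrent MIs" by arm, and a crude rate of all MI events; section 5.2 attaches 95% confidence intervals to the rate. The second tier of the exploratory win ratio in section 5.3.2 uses recurrent MI without the non-fatal restriction.

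**The concern.** Whether an MI counts in this analysis is settled by what happens in the 30 days after it. A patient whose only MI is fatal is censored at death as if free of MI or, in the competing-risk version, counted as a competing death. Neither treatment puts that MI back among the events.

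The invasive strategy could plausibly change how lethal an MI is as well as how often one occurs. The hazard ratio for non-fatal MI then mixes the two, and lower lethality moves it in the unfavourable direction, because MIs that would have been fatal become countable. This is the only MI hazard ratio in the main table, and readers will use it to judge the recurrent MI objective and to explain the composite.

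**Working it through.** **Inputs from the SAP.** The 30-day rule, the censoring rule, and the Cox and competing-risk models, all as cited above. No figure in the plan quantifies this point. The sample-size figures (HR 0.78, 752 events, 92.5% power) concern the composite, and nothing below rests on them.

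**Inputs that are assumed.** The documents give no MI case fatality, overall or by arm, so f0 and f1 are assumptions, shown as a range.

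**Formula.** If first MIs occur at hazard λ in the conservative arm and rλ in the invasive arm, first non-fatal MIs occur at about λ(1 − f0) and rλ(1 − f1). So

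HR for non-fatal MI ≈ r × (1 − f1)/(1 − f0),

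which exceeds 1 only if r > (1 − f0)/(1 − f1).

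**Results.**

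| f0 / f1 (assumed) | Multiplier | HR if r = 1.00 | HR if r = 0.90 | HR if r = 0.78 | HR > 1 only if r exceeds |
|---|---|---|---|---|---|
| 15% / 10% | 0.90/0.85 = 1.06 | 1.06 | 0.95 | 0.83 | 0.94 |
| 20% / 10% | 0.90/0.80 = 1.13 | 1.13 | 1.01 | 0.88 | 0.89 |
| 30% / 15% | 0.85/0.70 = 1.21 | 1.21 | 1.09 | 0.95 | 0.82 |

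If f0 = f1 the multiplier is 1. If MIs were more lethal in the invasive arm it would fall below 1.

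**Check by simulation.** Cox models were fitted to one simulated data set per scenario. Each had 50,040 patients per arm, 1 to 5 years of follow-up, and assumed yearly hazards of 0.10 for MI in the conservative arm, 0.08 for other CV death and 0.06 for non-CV death. The non-fatal MI HR divided by the any-MI HR was 1.06, 1.13 to 1.14 and 1.20 to 1.22 for the three pairs, in line with the formula. The any-MI HR itself returned r: 0.98 to 1.02, 0.89 to 0.91 and 0.78 to 0.79 for r = 1.00, 0.90 and 0.78.

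**Competing-risk version.** Treating death as a competing event changes how deaths enter the risk set, not which MIs are events. The dependence on case fatality remains.

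**Comparison within the SAP.** Time to first bleed covers BARC type 2 or higher and so includes fatal bleeds (type 5). Type 3 MI, which protocol v3.0 Appendix 16.1 defines by cardiac death, is among the types to be counted but in effect cannot enter the non-fatal MI analysis.

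**The case against.** The strongest reply is that the SAP introduces this analysis as a component of the composite, not as the answer to the recurrent MI objective. On that reading the objective is met by the counts and crude rates of all MIs by arm, which follows protocol v3.0 section 9.2.2, where recurrent MI is reported descriptively. A shift from fatal to non-fatal MI would be visible, because fatal, non-fatal and total MIs stand together in the secondary-events table and CV death stands beside non-fatal MI in the hazard-ratio table. The win ratio uses any recurrent MI, and the table note confines p-values to the primary outcome.

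Most of this stands, and it limits the weight of the point. What it does not supply is a comparative estimate. The crude rate counts repeat events, has no between-arm ratio specified, is not adjusted for frailty and does not handle death as a competing event. The win ratio is exploratory and merges MI with CV death.

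A reader might also infer that a strategy which makes MIs less lethal must appear to cause more of them. The documents do not support that. It requires similar MI incidence in the two arms and a sizeable difference in case fatality, and the documents report neither. At r = 0.78 the ratio stays below 1 in all three scenarios in the table.

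**Conclusion.** The point holds as a gap in a secondary analysis. No frailty-adjusted, between-arm estimate is planned for MI of any kind, and the one MI hazard ratio that is planned depends on survival after the event. With lower case fatality in the invasive arm, a reduction in MI is understated by a factor of 1.06 to 1.21 over the assumed range. Apparent harm arises only above the thresholds shown. With equal case fatality there is no distortion.

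It would be wrong to extend this to the primary result. In the composite a fatal MI is counted through the CV death, at most 30 days later, so the primary analysis is essentially unaffected.

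One related matter is unclear rather than wrong. Section 2.4 treats undetermined deaths as cardiovascular, both for the primary analysis and for the CV death outcome, whereas the fatal-MI rule refers to committee adjudication. The text does not settle whether an MI followed within 30 days by an undetermined death is fatal.

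**What to change.** In SAP sections 2.4 and 5.2 and in the time-to-event table, add time to first recurrent MI, fatal or non-fatal, dated at MI onset. Use the same frailty-adjusted Cox and competing-risk models, and name it as the comparative result for the recurrent MI objective. Keep time to first non-fatal MI as the component of the composite, to be read beside CV death. State in section 2.4 whether an undetermined death within 30 days makes an MI fatal, consistently with how undetermined deaths are handled for the primary and CV death outcomes.

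The cost is one extra secondary row and its models, without a p-value. Fatal and non-fatal MIs are already collected and adjudicated, and the primary endpoint does not change.

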#### Coronary angiography and coronary revascularisation

All coronary angiography and coronary revascularisation procedures occurring from the time of randomisation will be obtained from medical records and reported by site staff in the study database. Coronary angiography and revascularisation procedures performed as part of the trial intervention will not be included in this outcome measure. This will be instead be reported as described in Section 4.3.

Time to first (non-trial) coronary angiography and time to first (non-trial) coronary revascularisation procedure will be reported. Patients not experiencing the event will be censored at their date of death or date the they were last seen or assessed.

The total number of (non-trial) coronary angiography and (non-trial) coronary revascularisation procedures, and the total number of patients affected, will be calculated for each treatment group. The number of (non-trial) coronary angiography and (non-trial) coronary revascularisation procedures reported per participant will also be calculated. Crude rates will be calculated for each outcome measure as described above for recurrent MIs.

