Other previous studies have been non-randomized retrospective sub-group analyses or in the setting of chronic stable angina.(20) Two published studies have thus far evaluated the benefit of invasive strategy versus conservative treatment in older ( $\geq 75$  years) patients with ACS without stratification for frailty status and recruiting selected patient cohorts with no significant co-morbidities. In the first registry study, 1005 patients underwent coronary angiography and revascularisation, and 931 patients received conservative treatment. The mean age was 79 and 82 years ( $p < 0.0001$ ) respectively. In-hospital mortality and the combined endpoint of death or non-fatal re-infarction were lower in patients undergoing invasive management compared to those being managed conservatively (6.0% vs. 12.5%,  $p < 0.0001$  and 9.6% vs. 17.3%,  $p < 0.0001$  respectively). There was a marked reduction in one-year mortality in the invasive treatment group compared to conservative treatment group (OR 0.56; 95% CI 0.38-0.81).(21) The second study randomized 313 patients  $\geq 75$  years old with NSTEMI or unstable angina to an early invasive approach ( $n=154$ ) or initial conservative approach ( $n=159$ ).(22) In the early invasive treatment group, 88% of patients underwent coronary angiography and 55% had PCI, and in the initial conservative group it was 29% and 23% respectively. In patients with NSTEMI, there was a reduction in the primary endpoint (composite of death, MI, stroke and rehospitalisation for CV causes) in the early invasive treatment group compared to conservative approach at 1 year (HR 0.43; 95% CI 0.23-0.80, Log rank  $p < 0.05$ ). There was no difference noted between the two groups with unstable angina.

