|         |            | Added a supplementary analysis of the primary outcome which will include non-cardiovascular deaths as part of the composite outcome (i.e. non-fatal MI or death from any cause).      | The TSC suggested reporting a composite all-cause mortality and MI outcome as a subsidiary primary outcome measure at their meeting on 18//10/2021. Following a review of outcome measures used in other cardiovascular trials, and giving consideration to the Estimand framework, the TMG agreed to add an analysis of all-cause mortality and MI as a supplementary analysis of the primary outcome measure (the term 'supplementary' was chosen to use the same terminology as in the Estimand framework). |
|         |            | Definition of non-fatal MI added                                                                                                                                                      | To provide clarity as this was not previously defined                                                                                                                                                                                                                                                                                                                                                                                                                                                          |
|         |            | Clarified coronary angiography and coronary revascularisation outcome measures will exclude those performed as part of the trial                                                      | Clinical interest for this outcome measure is in the need for repeat procedures.                                                                                                                                                                                                                                                                                                                                                                                                                               |

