### 3.3 Analysis populations

**Intention to treat (ITT):** This population contains all patients randomised into the study (regardless of whether they were later found to be ineligible, a protocol violator, not receiving the allocated treatment etc.).

**Safety population:** This population contains patients in the intervention group undergoing their randomised coronary angiography.

Analysis of the primary endpoint and all secondary endpoints (apart from procedural and in-hospital complications) will be conducted in the ITT population. Procedural and in-hospital complications will be presented in the safety population.

There will be some participants allocated to the invasive strategy who do not undergo their allocated procedure and some participants allocated to conservative management who go on to receive coronary angiography. However, any analysis in a per-protocol population, of participants receiving their allocated treatment strategy as per-protocol, is likely to be biased as treatment assignment would no longer be random and there would likely be an association between treatment switching and the risk of a clinical event. Furthermore, treatment switching reflects real-life clinical practice and a per-protocol analysis of participants receiving their allocated treatment as per-protocol would not estimate real-life clinical effectiveness. For these reasons, it is not planned to conduct any analyses in a per-protocol population of participants receiving their allocated treatment strategy.

A per-protocol analysis, excluding any participants found to be ineligible after randomisation, may be conducted as a sensitivity analysis if the number of ineligible patients is found to be excessive (>2.5%).

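### The hazard ratios for non-trial angiography and revascularisation count early crossover in the conservative arm as outcome events but leave out allocated procedures in the invasive arm, so they mix non-adherence with later need

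*Supplement*

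**What the plan says.** SAP v2.0, section 2.4, sets the counting window: "All coronary angiography and coronary revascularisation procedures occurring from the time of randomisation will be obtained from medical records". It then applies the exclusion: "Coronary angiography and revascularisation procedures performed as part of the trial intervention will not be included in this outcome measure". The outcome takes this form: "Time to first (non-trial) coronary angiography and time to first (non-trial) coronary revascularisation procedure will be reported".

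Section 5.2 carries it into the analysis: "time to first (non-trial) coronary angiography and time to first (non-trial) revascularisation will be estimated using Kaplan-Meier methods". It continues: "Estimates of the treatment effect (HR) will be made using Cox regression models, as described above and reported with 95% CI's". Both outcomes have a row in the example table of primary and secondary time-to-event outcomes. A footnote says that trial procedures are left out, and p-values are kept for the primary outcome.

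The reason appears in the Document history entry for version 2.0: "Clinical interest for this outcome measure is in the need for repeat procedures".

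Three other places bear on this:

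- Section 2.1 defines the conservative strategy as medical therapy with no procedure.
- Section 3.3 expects "some participants allocated to conservative management who go on to receive coronary angiography" and discusses this as treatment switching. The Appendix (1.1) lists it as an intercurrent event for the primary estimand.
- Section 4.3.1 reports all procedures, trial ones included, in both arms within the first year. It adds Kaplan-Meier curves for time to first procedure, and an example table with rows from 7 days to 1 year.

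**The concern.** The exclusion reads as neutral, but only one arm has procedures that it can remove. Take an angiogram two days after randomisation. In an invasive patient it is the allocated treatment and is dropped. In a conservative patient whose clinician or family changed course it is a crossover, yet it enters the Cox model as a first event. Section 2.4 sets no common start after the index stay and no criterion of urgency or ischaemia that would separate the two.

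The stated interest in repeat procedures does not fit either, because a conservative patient's first angiogram repeats nothing. A hazard ratio below 1 would naturally be read as the invasive strategy sparing later procedures. Part or all of it could instead be early departure from allocation in the other arm.

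The boundary of the trial intervention is also loose. The treatment-received table refers to revascularisation arising from the randomised angiogram, but no time limit is given and staged PCI or later CABG is not addressed. Counting such procedures as non-trial would push the hazard ratio the other way.

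**Working it through.** The plan gives no rate, hazard ratio or power for these outcomes, so there is no figure to reproduce. The check asks what hazard ratio the counting rule returns when later need is truly the same in both arms.

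**From the documents**

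- Follow-up of at least 1 and at most 5 years (SAP 2.1), taken as uniform over that range.
- 1668 patients (SAP 2.5), so 1668/2 = 834 per arm.
- Procedures counted from randomisation, with allocated invasive procedures removed (SAP 2.4).

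**Assumed, because the documents give no value**

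- Yearly risk p of a later procedure: 3%, 5% or 10%, equal in both arms, with constant hazard λ = −ln(1 − p). For p = 0.05, λ = 0.0513 per year.
- Index-stay crossover c in the conservative arm: 0 to 15%, falling between days 0.5 and 7.
- Death as a competing event is not modelled.

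Later procedures count in every invasive patient, including those who skipped the allocated angiogram. A Cox model was fitted to 200,000 simulated patients per arm. The true hazard ratio for later need is 1.0 throughout.

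| Later risk per year | c = 0 | 2% | 5% | 10% | 15% |
|---|---|---|---|---|---|
| 3% | 0.99 | 0.81 | 0.63 | 0.45 | 0.34 |
| 5% | 1.01 | 0.87 | 0.74 | 0.57 | 0.46 |
| 10% | 1.01 | 0.93 | 0.84 | 0.71 | 0.61 |

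**Hand check of one cell (p = 5%, c = 5%).** In the invasive arm 14.1% have a counted procedure. The conservative arm should then have about 0.05 + 0.95 × 0.141 = 18.4%; the simulation gave 18.3%.

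**Would it look like an effect?** Events E = 834 × (0.183 + 0.141) = 270. The chance that the 95% interval excludes 1 is roughly Φ(|ln HR| × √(E/4) − 1.96) = Φ(0.301 × 8.22 − 1.96) = Φ(0.51), about 0.70 (0.71 with the unrounded hazard ratio). At 5% crossover this chance is 0.88, 0.71 and 0.50 for later risks of 3%, 5% and 10%. The formula assumes proportional hazards, which a cluster of events in the first week breaks, so these are rough figures.

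**All procedures counted.** With trial procedures included and 90% adherence assumed in the invasive arm, the same scenarios give hazard ratios from about 7 to 32. The two definitions can point in opposite directions on the same patients.

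**The case against.** Several points on the other side have weight.

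**Counting from randomisation is a legitimate intention-to-treat choice.** The objective is the effect of the strategy, section 3.3 says that switching is part of practice, and an early procedure after conservative allocation may be genuine failure of that strategy. This stands, and it is why the estimate should be kept. It does not make the estimate a measure of repeat or later need.

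**The rows are modest in status and labelled.** They are secondary, footnoted and without p-values. This limits the harm. The footnote does not tell the reader that conservative crossovers count, and a 95% interval excluding 1 will still be read as a finding.

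**Proportional hazards will be checked.** Section 5.2 requires this, with the time-dependent hazard ratio and restricted mean of section 5.1.2 as fallbacks. That may expose an early cluster of events. A restricted mean from randomisation would still include the crossovers.

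A reader might also draw stronger conclusions that the documents do not support:

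- *That the invasive arm contributes only repeat procedures.* Patients who skip the allocated angiogram, or are not revascularised after it, can later have a first procedure. In the earlier randomised trial described in Protocol v3.0, section 1, 55% of the invasive group had PCI, so 45% did not.
- *That the result favours the invasive strategy whatever happens.* With no index-stay crossover and equal later need, the hazard ratio is about 1.
- *That the plan hides the total number of procedures.* Section 4.3.1 shows them in both arms, with 7-day and 28-day rows that display early crossover. What is missing is an all-procedure hazard ratio in the main table.
- *That the distortion can be sized from that earlier trial.* There, for angiography and PCI, "in the initial conservative group it was 29% and 23% respectively". Setting these against an assumed 5 to 15% repeat rate gives ratios from ln(0.95)/ln(0.71) = 0.15 to ln(0.85)/ln(0.77) = 0.62. But the trial's figures are not split into index-stay and later procedures, the 23% is PCI only, and the repeat rate is assumed. The range mixes real need with artefact.

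**Conclusion.** The asymmetry follows from the SAP's own wording and needs no assumption. The exclusion acts on one arm, and an index-stay crossover in the other arm is an outcome event. With any such crossover, the hazard ratios shift towards the invasive strategy.

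The size is not known, because it depends on the crossover rate and the rate of later procedures. Under the assumed values, 5% crossover turns a true hazard ratio of 1 into 0.63 to 0.84. The loose boundary for staged procedures could offset some of this.

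The planned hazard ratios can describe procedures beyond the allocated strategy. On their own they cannot support a statement that the invasive strategy reduces later need. The change is worth making before analysis, but it concerns two secondary rows only.

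**What to change.** In SAP sections 2.4 and 5.2 and the main time-to-event table:

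1. Define which procedures belong to the trial intervention, covering staged PCI and CABG planned from the index angiogram, and give a time limit.
2. Keep the from-randomisation hazard ratios, but label them as procedures beyond the allocated strategy rather than repeat procedures.
3. Beside them, give the same hazard ratios from a common landmark in both arms, for example the 30 days from randomisation already used in section 5.3.2. Include everyone alive and under follow-up at that point, whatever was done before it. Report conservative-arm procedures before the landmark as crossover in section 4.3, and deaths before the landmark by arm.
4. Add the all-procedure comparison from randomisation over the full follow-up, trial procedures included.

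The cost is SAP wording and one derived time variable from procedure dates already collected. Deviations from allocated treatment are already recorded in the eCRF (Protocol v3.0, section 12).

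The landmark estimate conditions on survival to the landmark and moves early treatment failures into the crossover table, so it should accompany the from-randomisation estimate and not replace it. A fixed day is preferable to discharge, because allocation can affect when a patient goes home. Splitting crossovers by reason may not be possible: the SAP's example tables list reasons only for invasive patients who missed their angiogram.
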